### CR intervention

The manualised Cognitive Remediation in Drug and Alcohol Services (CRiDAS) program will be used for CR, which consists of 12 one-hour group-based sessions that will take place across 6 weeks (two sessions per week). Each session will be dedicated to strategy training, which includes traditional instructional pedagogical approaches, group discussion/reflection and exercises to demonstrate concepts. The CR intervention was developed with a strong emphasis on the training of EF in view of the finding that EF is particularly impaired in an AOD treatment population. Barkley’s evolutionary model of EF [52, 53] was used to structure a large part of the program. The CR program will use a “top-down” approach, including training in compensatory strategy use with a particular emphasis on EF. The modules cover the following topics: brain functioning, attention, memory, visual and verbal working memory, emotion regulation, decision-making and problem-solving. Facilitators will be staff of the residential AOD treatment sites who will undergo training to administer the intervention, and will be chosen by service management on the basis of a minimum skillset relevant to program delivery. Facilitators will be trained immediately prior to introducing the intervention, to prevent staff from utilising CR techniques during phases of TAU.

Intervention facilitators will take attendance for each module of the intervention in order to monitor adherence and dose of the intervention. An independent researcher/clinician will use the CRiDAS treatment fidelity measure (to be developed) to measure fidelity via audio/video recordings of 10% of the sessions at each site.

### Assessment measures

See Table 2 for an outline of the timeline of assessment measures. To provide an estimate of the overall level of premorbid intellectual functioning, the Test of Premorbid Functioning [54] will be administered once only, at the first test phase. One primary outcome measure will be an inventory-based measure of EF, as previous findings have shown that inventory-based assessment is more strongly associated with real-world functioning outcomes in SUD than performance-based assessment [36]. Given the high rates of treatment drop-out in residential AOD treatment services, another primary outcome measure will be the length of treatment retention, measured as time in treatment as a proportion of program duration [4]. This is because the program duration may vary across services. Secondary outcome measures will evaluate substance use severity, health service utilisation, individual goal-attainment, quality of life, treatment satisfaction, and performance-based measures of EF. An economic analysis will also be undertaken to evaluate the costs associated with delivering CR versus TAU. Data collection will be facilitated by research assistants blinded to the randomised condition, that is, whether or not a site has implemented cognitive remediation.

**Table 2 Tab2:** Timeline of Assessment Measures

Domain assessment and instrument used	Baseline Assessment	During Intervention	Post-TAU/CR	Follow-Up	Post-trial
Mini International Neuropsychiatric Interview or DSM-V	X				
Drug and Alcohol Cognitive Impairment Screening Tool (DACIST)	X				
Australian Treatment Outcomes Profile (ATOP)	X			X^a^	
Severity of Dependence Scale (SDS)	X		X	X	
Test of Premorbid Functioning	X				
Behaviour Rating Inventory of Executive Functioning – Adult Version (BRIEF-A)	X		X	X	
Kessler Psychological Distress Scale Plus (K10+)	X		X	X	
Quality of Life Enjoyment and Satisfaction Questionnaire – Short Form (Q-LES-Q-SF)	X		X	X	
Patient-Reported Outcomes Measurement Information System Global 10 (PROMIS Global-10)	X		X	X	
Brief Self-Control Scale	X		X	X	
EUROQOL – EQ-5D (EQ-5D)	X		X	X	
EUROHIS-QOL 8	X		X	X	
Q-LES-Q-SF	X		X	X	
Alpha Span Task	X		X	X	
Symbol Digit Modalities Test (SDMT)	X		X	X	
Goal Attainment Scale 2.0 (GAS 2.0)	X		X	X	
Brief Executive Assessment Tool (BEAT)	X		X	X	
Stroop Task	X		X	X	
Five-Point Test	X		X	X	
Group Session Rating Scale		X			
Feasibility/satisfaction questionnaire (staff and clients)					X
Time in Treatment (for individuals)					X
Mean Length of Stay as a proportion of program duration for sites	X				X
Health Service Utilisation					X
Economic Analysis					X

Notes: ^a^ = Post-discharge follow-up only

Outcome measures will be taken at intake, the test phases (2 week periods pre- and post- TAU/CR phases), and follow-up (2 months, 4 months, 6 months and 8 months following completion of a TAU/CR phase). Attempts to improve follow-up rates in the current study will include using telephone interviews and online questionnaires at follow-up to administer some of the assessments if necessary.

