## Background

Substance use disorder (SUD) is a major global health problem, which has increased notably in the last few years [1]. In Australia, a recent publication reported that one in 200 people in the general population received treatment for substance use in 2014–15, which represents a 6% increase from the previous year [2]. Although SUD is frequently described as a chronic and relapsing condition, favourable long-term outcomes are consistently associated with alcohol and other drug (AOD) treatment completion [3]. However, failure to complete treatment, or “drop-out”, is very common in both inpatient and outpatient treatment services [4, 5].

According to a systematic review of the literature, one of the major risk factors of drop-out from AOD treatment is cognitive impairment [6]. Over the last two decades, neuropsychological research has consistently shown that substance use is associated with a significant degree of impairment in cognitive functioning. Whilst specific aspects of cognitive functioning may predate and influence the initiation of AOD use [7], increased substance use results in a greater degree of impairment [8, 9]. That is, there is a strong association between the quantity and duration of AOD use and the degree of cognitive dysfunction. Cognitive deficits in individuals with SUD may be further exacerbated by the presence of common comorbidities such as traumatic brain injury and psychiatric disorders [10, 11]. Although partial recovery of cognitive impairment may occur after immediate cessation of AOD use, many cognitive deficits fail to recover following withdrawal and abstinence [12, 13]. For example, it has been estimated that approximately 50–80% of recently detoxified individuals with SUD are cognitively impaired when assessed with the Montreal Cognitive Assessment [14–17].

In individuals with SUD, the most prominent cognitive deficits are seen in executive functioning (EF) [9, 18]. EF abilities (such as working memory, planning and organisational skills, reasoning, and self-regulation) are mediated by the frontal cortex, an area of the brain that is particularly vulnerable to substance-related impairment [19]. Common AOD treatment interventions, including counselling and psychoeducation, are heavily reliant on intact EF abilities in order to identify, promote and achieve successful behavioural change [20, 21]. Thus, EF impairment significantly predicts treatment drop-out and relapse [22–24].

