Site 8		TAU 1		TAU 2		TAU 3		Cog Rem 1		F/U Period	
Site 9		TAU 1		TAU 2		TAU 3		Cog Rem 1		F/U Period	
Site 10		TAU 1		TAU 2		TAU 3		Cog Rem 1		F/U Period	

Note: *Cog Rem* Cognitive Remediation Phase, *TAU* Treatment-As-Usual Phase, *F/U Period* Follow Up Period

The estimated number of participants is based on prior research in NSW residential drug and Alcohol Treatment [42]. *Discharge* refers to the discharge of participants from the residential treatment service (either through completing the program or self-discharge/drop out before the completion of the program). *Attrition* refers to drop-out from the study or otherwise being non-contactable following discharge from the treatment service.Each site will start with *n* = 20 participants on average;Within a single cohort, there will be:a 40% discharge rate over each six-week TAU/CR phase plus two-week test phase;a 65% discharge rate over the following 2 months;an 80% discharge rate over the following 4 months;a 90% discharge rate over the following 6 months; anda 95% discharge rate over the following 8 months;New clients will enter a service at the same rate as other clients leave the service;If a client enters a service during a TAU/CR phase, they will delay their participation in the trial until the next test phase;Some clients will participate in more than one CR phase;All participants who have completed at least one TAU/CR phase will be eligible for follow-up testing, which will occur at test phases 3, 4, 5 and 6.If a participant has had a CR phase they are ineligible for TAU follow-up.If a participant has had more than one CR phase they will still be eligible for CR follow-upFollow-up attrition rates have been estimated to be:65% attrition at two-month follow up75% attrition at four-month follow up85% attrition at six-month follow up90% attrition at eight-month follow up

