### Primary outcome measures

#### Behavior Rating Inventory of Executive Function – Adult Version (BRIEF-A) [55]

The BRIEF-A is a 75 item self-report questionnaire consisting of nine subscales. The Global Executive Composite (GEC) provides an overall summary score and will be a primary outcome variable.

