### Statistical methods

#### Sample size estimation

The primary outcome is the BRIEF-A GEC difference score between pre- and post-TAU/CR phase. Given previous data for a more comprehensive 24 h CR program [42], sample size calculations were based on a difference in BRIEF-A score of 2.25 for the current 12 h program. We used the sample size methodology for stepped wedge designs put forward by Hooper et al. [75]. Assuming a standard deviation of 5.15, obtained from the Marceau data [42], an individually randomised trial would require a total sample of 165 people in order to have 80% power to detect the intervention effect at the 5% significance level. The design effect for cluster randomisation, assuming an intraclass correlation of 0.05 and anticipating 20 people per cluster, is 1.95 and the design effect for repeated assessment, assuming a cluster autocorrelation of 0.5, is 0.534. The required number of clusters for this stepped wedge design is therefore nine. In order to account for a 10% loss of the total sample to follow-up, (e.g participants that are discharged and not replaced by new participants in the research) and to protect against the possibility of a cluster withdrawing from the trial, an additional cluster will be recruited yielding a total of 10.

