A significant challenge in this trial is the high rate of unplanned drop-out that is common in residential AOD treatment services. According to recent figures, approximately 20% of individuals with SUD unexpectedly cease treatment [2]. To help address this concern, compensatory CR will be delivered in one-hour sessions, twice a week, over a six-week period, which is a reasonable amount of time to expect individuals to dedicate to the intervention. A further challenge will be retaining participants at follow-up. Attempts to improve follow-up rates in the current study include using telephone and online follow-up to administer some outcome assessments, obtaining contact details of significant others to help with locating participants and reinforcing the importance of conducting follow-up to participants.

The current study will be the first stepped wedge cluster randomised trial of a compensatory CR intervention in a residential substance abuse population. The study seeks to address a significant gap in the literature by examining the effectiveness of implementing a six-week CR group program within AOD residential treatment programs. It is expected that following completion of CR, participants will demonstrate significantly improved EF and treatment retention rates, reduced AOD use and health service utilisation rates, as well as achievement of individually-set goals, quality of life, and treatment satisfaction.

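### Residents discharged during their first TAU/CR phase have no stated route to a post-phase BRIEF-A, although it is self-completed and remote contact is already planned

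*Protocol article*

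**What the plan says.** Assessment measures (text below Table 2) schedules outcomes at intake, at the two-week test phases around each TAU/CR phase, and at follow-ups two to eight months "following completion of a TAU/CR phase". Remote administration is mentioned there only for follow-up: measures to raise follow-up rates "will include using telephone interviews and online questionnaires at follow-up to administer some of the assessments if necessary". Strengths and limitations repeats this, again under retention at follow-up: "using telephone and online follow-up to administer some outcome assessments".

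The assumptions below Table 1 (Study design) say who enters follow-up: "All participants who have completed at least one TAU/CR phase will be eligible for follow-up testing", at test phases 3 to 6. The same list expects "a 40% discharge rate over each six-week TAU/CR phase plus two-week test phase".

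On the outcome itself, the Primary outcome measures section states: "The BRIEF-A is a 75 item self-report questionnaire consisting of nine subscales". Sample size estimation uses the pre- to post-phase change in its Global Executive Composite. It allows for a 10% loss, exemplified by "participants that are discharged and not replaced by new participants in the research". The Analysis plan is intention-to-treat, with all participants brought in through a multiple-imputation sensitivity analysis. Table 2 schedules the BRIEF-A at baseline, post-TAU/CR and follow-up.

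**The concern.** Read together, these rules leave a gap. Remote collection belongs to follow-up, and follow-up belongs to people who have completed a phase. Someone who leaves in week 5 of a first phase has a baseline BRIEF-A and nothing planned after it. Someone who leaves just after the phase ends can be contacted at two months.

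The loss is unlikely to be random. The Background says that "EF impairment significantly predicts treatment drop-out and relapse". Retention is also the other primary outcome and is expected to improve under cognitive remediation. If the intervention keeps more impaired residents in treatment, the people who supply a post-phase score will differ between conditions. Replacing leavers with new entrants restores the number of scores but not the population that started the phase. Multiple imputation would have only pre-discharge data for these people. Scores that were never collected cannot be recovered by a later analysis plan.

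**Working it through.** **1. The plan's own sample size.** Inputs (Sample size estimation): difference 2.25, SD 5.15, 5% significance (taken as two-sided), 80% power, ICC 0.05, 20 per cluster, cluster autocorrelation 0.5.

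- Individually randomised total: 4 × [5.15 × (1.960 + 0.842) / 2.25]² = 164.5. The plan states 165.
- Clustering: 1 + 19 × 0.05 = 1.95, as stated.
- Repeated assessment, three sequences and four periods, r = 20 × 0.05 × 0.5 / 1.95 = 0.256: design effect 0.5345. The plan states 0.534.
- Clusters: 165 × 1.95 × 0.534 / 20 = 8.59, so nine, plus one spare.

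The arithmetic reproduces, so the point does not rest on an error there.

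**2. Who has no route.** Ten sites start with 20 residents each, and 40% (8 per site) are replaced at each of the three later phases.

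- Recruits: 200 + 3 × 80 = 440, the article's figure.
- Discharges over four phases: 10 × 4 × 8 = 320 of 800 person-phases.
- Discharges during a person's first phase: 0.40 × 440 = 176. The 10% allowance corresponds to 44.
- Discharges after an earlier completed phase: 320 − 176 = 144. These people are eligible for follow-up at test phases 3 to 6, which fall at the end of Periods 2 to 5.
- Of the 144, about 48 leave in the phase in which their site switches to cognitive remediation (10 sites × 12 carried over × 0.40). If their follow-up status is treated as unclear, 96 remain.

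The 40% covers eight weeks, including the test phase. Anyone assessed before leaving within the test phase does have a score, so 176 is towards the upper end.

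**3. What could be recovered.** The document gives no contact rate for early leavers. As an assumption, take 35%, the complement of the plan's 65% attrition at two months: 0.35 × 176 = 61.6, about 62 scores. At 20% it is 35, and at 50% it is 88.

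**4. Power.** Generalised least squares with the 3/3/4 site layout, four post-phase periods, period effects and the plan's variance inputs. This assumes that 20 per cluster means residents who start a phase, so 12 per site-phase remain resident. Recovered scores are spread over 40 site-phases.

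| Scores per site-phase | How obtained | Power |
|---|---|---|
| 12 | no leavers measured | 73.5% |
| 12.84 | 35% of the 96 | 75.4% |
| 13.26 | 35% of the 144 | 76.3% |
| 13.54 | 35% of the 176 | 76.8% |
| 14.8 | 35% of all 320 | 79.1% |
| 20 | everyone measured | 85.9% |

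Adding the 176 first-phase leavers to a base of 12 gives 73.5% to 76.8%, a gain of 3.3 points. If the earlier completers already supply scores, full coverage gives 76.3% to 79.1% (2.8 points), or 75.4% to 79.1% (3.7 points) from the base with 96. Recovering the 176 from a base of 12 gives 75.5% at 20% reach and 78.1% at 50%.

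**The case against.** The strongest reply has four parts.

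**Not all leavers are missed.** A reader might infer that the BRIEF-A is never sought from anyone discharged during a phase. That would put 320 person-phases at stake, with about 112 recoverable (0.35 × 320) and power rising from 73.5% to 79.1%. The document does not support this. The 144 who had completed an earlier phase are eligible for follow-up, where the BRIEF-A is scheduled and remote contact is allowed. This objection stands, and it limits the point to first-phase leavers. What remains for the 144 is that nothing says a follow-up score may serve as the post-phase value of the later phase they started.

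**Nothing forbids contact.** The text does not say that test-phase assessments must be on site. It separates discharge from attrition, and it plans to collect contact details of significant others. A journal article also condenses contact procedures. This is fair: the gap is inferred, and it is not a stated prohibition. But the article does state where remote collection applies, twice, and who enters follow-up. Followed as written, those rules leave first-phase leavers out.

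**Planned completers.** Because discharge is defined to include programme completion, one might infer that many leave mid-phase by plan and could fill in an exit form. The Abstract restricts invitation to those expected to stay for the six weeks, and Study setting requires programmes of at least 10 weeks. Planned completion within a first phase should therefore be uncommon, and no separate exit form is proposed.

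**The benefit is uncertain.** The 35% is drawn from phase completers, and early leavers may be harder to reach. Those reached are themselves selected. Only some assessments are to go remote, and the BRIEF-A is not named among them. The power model leaves out the baseline covariate and the individual random effect in the Analysis plan. If 20 already means people with data, power is about 86% and the precision argument falls away. All of this stands as limits on the size. The selection argument does not depend on the meaning of 20.

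**Conclusion.** The point holds for residents discharged during their first TAU/CR phase. They are about 40% of participants, some 176 of 440 on the plan's own figures, and no post-phase BRIEF-A route is stated for them. At an assumed 35% reach about 62 scores would be recovered (35 to 88 for 20% to 50%). The power gain is roughly 3 to 4 points, conditional on 20 per cluster meaning residents who start a phase. The more important gain is reduced selection in the primary comparison, together with direct evidence on how leavers differ from stayers. Its size depends on that difference, which the document does not give. This is a worthwhile, inexpensive improvement to a collection rule. It is not an error in the sample size calculation.

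**What to change.** In Assessment measures and Table 2, extend telephone and online administration of the BRIEF-A, by name, to the post-TAU/CR assessment. Seek it at the test phase closing the phase for everyone who started that phase, whether or not they are still resident. State that, for someone who completed an earlier phase and left during a later one, a BRIEF-A taken at that test phase counts as the post-phase value for the phase they started. Analyse these scores under intention-to-treat by the site's condition for that phase. Record mode of administration and residence status, and use both in a sensitivity analysis.

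The cost is a wording change and at most about 80 contact attempts per test phase (10 sites × 8 leavers), using the research assistants and contact methods already planned. The downside is that some scores will come by another mode and from people living outside the service, which is why both must be recorded and examined.

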### Primary outcome measures

#### Behavior Rating Inventory of Executive Function – Adult Version (BRIEF-A) [55]

The BRIEF-A is a 75 item self-report questionnaire consisting of nine subscales. The Global Executive Composite (GEC) provides an overall summary score and will be a primary outcome variable.

#### Time in treatment

Duration of treatment will be provided by the Alcohol and Other Drug Treatment Services National Minimum Data Set [56]. Time spent in treatment (length of stay) as a proportion of program duration will be used as a primary outcome variable.

### Secondary outcome measures

#### Severity of Dependence Scale (SDS) [57]

The SDS is a 5-item questionnaire which assesses for severity of substance use. The outcome variable will be total score.

#### Health service utilisation

For each participant, the number of visits to health services in the year prior to and following commencement of CR will be compared. These data will be obtained from linking data obtained from this study with four other datasets (NSW Admitted patient data collection, NSW Emergency Department data collection, NSW Cause of death unit record file, NSW mental health ambulatory data collection). Data linkage will be undertaken by the Centre for Health Record Linkage. Variables of interest will include medical centre, hospital and emergency room admissions, access of community-based mental health and AOD services, and mortality rates.

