### The current study

The study will aim to examine the effectiveness of adding a CR intervention to TAU on two primary outcomes, being:A self-report inventory of executive functioning; andTreatment retention

The study will also assess the impact of CR in addition to TAU on a number of secondary outcomes:AOD useHealth service utilisationFunctional goal attainmentQuality of lifeClient satisfaction with treatmentPerformance-based measures of EFEconomic analysis

The study will be conducted as a stepped wedge randomised cluster trial. Stepped wedge designs are increasingly being utilised in the evaluation of interventions within routine treatment services and are recommended where there are limited numbers of clusters [48–50]. The study is funded by the NSW Agency for Clinical Innovation.

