## Methods/design

### Study setting

The research program will be conducted at ten residential treatment facilities run by non-governmental organisations in NSW, Australia. All organisations will be abstinence-based however a portion of residents may be prescribed medications or opioid substitution treatments (OST) (e.g. methadone). Limited leave from the residential facilities, close observation by staff and other residents, and random urine tests will ensure abstinence from substances while participants are enrolled in treatment programs. Services that accommodate at least 15 residents and have a minimum project duration of 10 weeks will be invited to participate in the study.

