### Study design

The proposed study will be conducted as a prospective stepped wedge cluster randomised trial, where randomisation will occur at the cluster level. The design involves random and sequential crossover of clusters from TAU to CR until all clusters have implemented CR (Table 1). TAU was selected as the comparator condition as the CR intervention must be demonstrated to be effective above and beyond what residential AOD services are currently offering in order to be useful as an adjunct treatment. There will be four six-week phases of either TAU or CR, interspersed by two-week test phases, at each of the ten sites. The order in which the sites receive cognitive remediation will be generated by an independent statistician using computer-generated randomisation. After the initial two-week assessment phase (weeks 1–2), all clusters will undergo 6 weeks of treatment as usual (weeks 3–8). Following the second two-week assessment phase (weeks 9–10) clients at the three sites randomised to start first will receive CR for a period of 6 weeks (weeks 11–16), then this treatment will continue for the life of the study. After the next two-week test phase (weeks 17–18), another 3 sites will be randomly selected to commence CR, and so on until all services have provided CR. Six weeks after the final post-intervention phase (weeks 33–34) an additional two-week testing phase will be allocated for follow-up (weeks 41–42). CONSORT procedures will be followed including using an intention to treat analysis [51].

**Table 1 Tab1:** Progression of sites from Treatment as Usual to Cognitive Remediation In Stepped Wedge Design

	Test Phase 1	Period 1	Test Phase 2	Period 2	Test Phase 3	Period 3	Test Phase 4	Period 4	Test Phase 5	Period 5	Test Phase 6
Week	1–2	3–8	9–10	11–16	17–18	19–24	25–26	27–32	33–34	35–40	41–42
Site 1	Test Phase 1	TAU 1	Test Phase 2	Cog Rem 1	Test Phase 3	Cog Rem 2	Test Phase 4	Cog Rem 3	Test Phase 5	F/U Period	Test Phase 6
Site 2		TAU 1		Cog Rem 1		Cog Rem 2		Cog Rem 3		F/U Period	
Site 3		TAU 1		Cog Rem 1		Cog Rem 2		Cog Rem 3		F/U Period	
Site 4	Test Phase 1	TAU 1	Test Phase 2	TAU 2	Test Phase 3	Cog Rem 1	Test Phase 4	Cog Rem 2	Test Phase 5	F/U Period	Test Phase 6
Site 5		TAU 1		TAU 2		Cog Rem 1		Cog Rem 2		F/U Period	
Site 6		TAU 1		TAU 2		Cog Rem 1		Cog Rem 2		F/U Period	
Site 7	Test Phase 1	TAU 1	Test Phase 2	TAU 2	Test Phase 3	TAU 3	Test Phase 4	Cog Rem 1	Test Phase 5	F/U Period	Test Phase 6

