### Analysis plan

Baseline characteristics will be summarised using means and standard deviations or frequencies and percentages as appropriate. The primary outcome variable will be the BRIEF-A GEC score and the effect of the intervention will be estimated using a linear mixed model. The model will include the baseline BRIEF-A GEC as a covariate and a fixed effect for each time period after baseline to account for any secular trends. We will also include random effects for treatment centre, time within centre and individual within centre to account for the clustering, repeated measurements on centre and repeated measures on individuals, respectively. The main predictor of interest will be a pre−/post-intervention variable, which will measure the overall effect of the intervention. The data will be analysed according to the intent-to-treat principle, with sensitivity analysis undertaken to include all participants under an appropriate multiple imputation model for the missing data.

Two analyses are proposed to investigate the impact of CR on treatment retention, being:Direct analysis of retention (proportion of time spent in treatment relative to program duration) across TAU and CR conditions; andComparison of historical retention data (dating back 2–5 years) with retention rates following the first CR phase for each site. A 10% increase in service retention rate will be the indicator of a clinically meaningful gain.

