## Discussion

EF impairment is a significant predictor of treatment drop-out for individuals with SUD. There is an opportunity for AOD treatment providers to address cognitive impairment as part of routine care in order to potentially increase treatment efficacy and reduce treatment drop-out. The present study aims to examine the effectiveness of providing a group-based compensatory CR intervention as an adjunct to residential AOD treatment programs. It is expected that compared to pre-intervention, participants will demonstrate a significant improvement in EF and the duration of treatment retention. In addition, it is anticipated that there will be reductions in harmful AOD use and associated health service utilisation, as well as significant improvements in personal goal achievement, quality of life, and treatment satisfaction. As the current study is the first stepped wedge cluster randomised trial of a compensatory CR intervention within a residential AOD population, the results potentially hold important implications for the way that interventions are delivered across treatment settings.

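### Health service use is compared before and after starting CR with no TAU comparator, so the stated comparison cannot estimate the effect of CR in addition to TAU

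*Protocol article*

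**What the plan says.** The Health service utilisation paragraph, under Secondary outcome measures, defines the comparison: "For each participant, the number of visits to health services in the year prior to and following commencement of CR will be compared". It names four linked datasets and lists admissions, community service contacts and mortality as variables of interest. It mentions no TAU group and no adjustment for calendar time or time since admission.

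The section The current study places this outcome on a list introduced by "The study will also assess the impact of CR in addition to TAU on a number of secondary outcomes". The Study design section gives the reason for the control condition: "TAU was selected as the comparator condition as the CR intervention must be demonstrated to be effective above and beyond" what services already offer. The Discussion states the expectation: "it is anticipated that there will be reductions in harmful AOD use and associated health service utilisation".

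The Analysis plan gives BRIEF-A a mixed model with period effects. For retention it proposes "Direct analysis of retention (proportion of time spent in treatment relative to program duration) across TAU and CR conditions", alongside a historical comparison. It says nothing about health service use.

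**The concern.** The aim concerns CR on top of TAU, but the stated comparison contains no TAU experience except what the same person had before starting CR. Anyone who never starts CR has no index date and cannot enter it.

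Use may well fall around this index date without any CR effect. The year before includes the run-up to a residential admission. The year after includes time in a setting of which the Study setting section says: "Limited leave from the residential facilities, close observation by staff and other residents, and random urine tests will ensure abstinence". TAU continues alongside CR, and calendar time moves on. A before/after contrast cannot separate these influences from CR.

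At stake is whether an anticipated reduction in utilisation can be attributed to CR at all. Mortality, listed under the same outcome, cannot be compared before and after in the same person.

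**Working it through.** **Inputs.** Study design section: "Each site will start with *n* = 20 participants on average"; "a 40% discharge rate over each six-week TAU/CR phase plus two-week test phase"; leavers are replaced at the same rate, and newcomers wait for the next test phase. Table 1: CR starts in week 11 at Sites 1–3, week 19 at Sites 4–6 and week 27 at Sites 7–10. Participants section: about 440 recruited.

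**1. Reproduce the 440.** Ten sites × 20 = 200 at Test Phase 1. Replacements are 20 × 0.40 = 8 per site, or 80 at each of Test Phases 2, 3 and 4. Total 200 + 3 × 80 = 440, as stated.

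**2. Condition at entry.**

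| Entry point | TAU | CR |
|---|---|---|
| Test Phase 1 | 200 | 0 |
| Test Phase 2 | 7 × 8 = 56 | 3 × 8 = 24 |
| Test Phase 3 | 4 × 8 = 32 | 6 × 8 = 48 |
| Test Phase 4 | 0 | 80 |
| Total | 288 | 152 |

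**3. Participants who never start CR.** Each site loses 8 people per TAU phase. Sites 1–3 have one such phase, Sites 4–6 two and Sites 7–10 three: 8 × (3×1 + 3×2 + 4×3) = 8 × 21 = 168. As a share, 168/440 = 38%. If the article's later rates of 65% and 80% are instead read as cumulative discharge over successive phases, the count is 170.

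**4. Crossover.** TAU entrants who later receive CR: 288 − 168 = 120, which is 120/288 = 42%. The longest wait is from week 3 to week 27, or 24 weeks, so all cross within the one-year window.

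**5. Concurrent information.** Only Test Phases 2 and 3 have entrants under both conditions: CR 24 + 48 = 72, TAU 56 + 32 = 88, together 160 of 440.

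**6. Bias when CR does nothing (assumed inputs).** The article gives no visit rates. Suppose use drops by a fraction f at the start of a person's first phase and stays there. Someone with w weeks in TAU phases before CR has a before-year level of 1 − f × w/52 and an after-year level of 1 − f. The apparent fall is 1 − (1 − f)/(1 − f × w/52). With f = 20%:

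- w = 0 (enters directly into CR): 20.0%
- w = 8: 1 − 0.8/0.969 = 17.5%
- w = 16: 1 − 0.8/0.938 = 14.8%
- w = 24: 1 − 0.8/0.908 = 11.9%

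So the bias depends on the randomised sequence and does not vanish.

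**7. False-positive rate (assumed inputs).** A simulation of 2,000 runs per setting used no CR effect, 270 CR and 170 TAU participants, a mean of 2 or 4 visits a year and overdispersed counts. It ignored clustering and placed the whole natural fall after the index date, which is the unfavourable case.

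| Natural fall | Before/after comparison, p < 0.05 |
|---|---|
| 0% | about 5% |
| 10% | 16–20% |
| 20% | 56–64% |
| 30% | 90–95% |

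Comparing the change in CR with the change in TAU gave about 4–5% throughout, with an estimate near zero.

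**The case against.** The sentence stands under outcome measures, not under the Analysis plan, and an article commonly leaves models for secondary outcomes to the SAP. It could be read as defining a change score per person, to be contrasted between conditions later. That would be a fair defence if the index date were neutral. It is not: commencement of CR is undefined for people who had only TAU, so no TAU change score can be formed from this definition. The article has therefore fixed a comparison, and it conflicts with the article's own aim.

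It also counts that this is one of seven listed secondary outcomes and that both primary outcomes have a TAU/CR contrast. No primary conclusion depends on this sentence.

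A reader might infer more than the document supports:

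- **The entire natural decline would appear as a CR effect.** CR start is not admission. Newcomers wait for the next test phase, and about 120 participants spend at least one TAU phase in residence first, so some of the decline lands in the before year. Only part of it is miscredited.
- **Linked records are the only outcome that escapes the 65–90% follow-up attrition.** Time in treatment, a primary outcome, comes from an administrative dataset and needs no follow-up contact. Linkage itself requires separate consent.
- **A clean randomised comparison of 288 with 152 is available.** About 42% of the 288 receive CR within the year, and only 160 entrants fall in periods containing both conditions.
- **The design cannot separate CR from TAU.** The stepped wedge can; the analysis as written does not.

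**Conclusion.** The comparison is wrong as written and should be fixed. It omits the comparator the trial names, and about 38% of planned participants would fall out of it. That share rests on the article's own turnover figures, with 40% discharge per phase applied throughout.

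The direction of the concern is clear: any fall from admission, residence, TAU or time would partly be credited to CR. Its size is unknown. The false-positive rates and apparent falls above illustrate the mechanism under assumed inputs and are not forecasts. The point affects what may be concluded about utilisation, not the primary outcomes.

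**What to change.** State in the protocol or SAP:

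- **Index date.** The start of the first TAU or CR phase entered, for every participant who consents to linkage.
- **Main comparison.** Subsequent visit counts by the site's randomised condition at entry, in a count mixed model (for example negative binomial) with prior-year count as covariate, fixed entry-period effects, a random site effect and time at risk as offset. This is the intention-to-treat estimate.
- **Crossover.** A supporting analysis with CR as a time-varying exposure.
- **Before/after change around CR start.** Descriptive only, with no claim of a CR effect.
- **Mortality.** A between-condition comparison.

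Comparing CR starters with the 168 who left early would not be a substitute, because it selects on retention.

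Cost: mainly a change of analysis wording. The linkage request must also cover participants who never start CR, which the present definition of the data window does not secure. The by-entry estimate will be diluted by crossover and imprecise, and the report should say so.
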